### Intervention description

#### The rural response system (RRS)

The RRS was developed by the Gender Studies and Human Rights documentation Centre (Gender Centre) in 2002 to address some of the key findings from its 1998 study on VAW and children in Ghana [7]. The research also showed that VAW was not seen as a crime but was viewed as a private matter that should be taken care of within the family [7]. Owing to this outlook, interventions were an intrusion into a private situation. This societal view consequently inhibited women from talking about their experiences of violence. When women chose to talk about their experiences of violence, they preferred to report informally to family, friends or members of the community [7]. The 1998 study by Gender Centre also revealed a lack of support for victims of violence; such that when women did report violence committed against them, state agencies were the least likely venue for them to report [7]. The women believed that the attitude of state agency personnel, with the same biases as the society in which they operate, tended to reflect in how they responded to cases of violence [7]. While this lack of support was evident throughout the country, it was more so in the rural communities. The RRS was subsequently developed by the Gender Centre as a strategy to deal with four major problem areas prioritised from the research findings [7]. These were (i). The poor state/institutional response to VAW, with frequent patterns of victim blaming, referring reported cases back to family and state agency personnel and society in general trivialising the issue; (ii). The high degree of tolerance of VAW in Ghanaian society, perpetuated by strong perceptions that domestic violence, i.e. violence that occurs in the home and in intimate relationships – is a private/family matter and not a serious crime; (iii). General confusion about what constitutes violence and ignorance about the causes, consequences and mechanisms that perpetuate VAW; and finally, (iv). Isolation of rural women and women’s expressed dissatisfaction with the assistance and support they received when they reported VAW cases.

While the RRS intervention model was developed to respond to the problem areas prioritised from the research findings, it was inspired by the City of Duluth’s Coordinated Community Response (CCR) to Domestic Violence ‘The Duluth Model’ [13]. At the heart of the CCR is a shared understanding by all state and non-state partners involved that VAW women is a crime and a human rights violation and that the response to it must prioritise the safety and autonomy of the survivor. The RRS intervention is comprehensively described in the Gender Centre publication titled ‘A Guide to Developing a Community Response to Violence against women in Ghana’ [7]. Figure 3 shows the intervention logic model guiding our intervention delivery. As part of the RRS system, community-based action teams (COMBAT) are selected by community members and trained by the Gender Centre to create awareness on gender-based violence (GBV) and provide support to victims who report to them. The RRS operates on the theory that progressive change does not happen overnight. Ingrained norms and learned behaviours need sustained and cumulative interventions over long periods of time to deliver results. Representatives from State Agencies are also trained to aid them to respond effectively to cases that are brought before them. The overall result intended is a reduction of IPV, characterised by the improved well-being of women and men and the reduced victimisation of women in Ghana.

**Figure 3. F0003:**
[figure not shown]
Intervention logic model to reduce incidence of violence against women in Ghana.

#### Community based action teams (COMBAT)

The RRS is stressed as a community initiative facilitated by the Gender Centre to foster community ownership. The selection of the COMBAT, the criteria for the selection of COMBAT and their roles are done by the community members with the Gender Centre serving only as a facilitator in this process. A COMBAT should be somebody who can keep confidences; that he/she is not known to be violent himself or herself; that he/she is somebody well respected in the community; and that he/she has the spirit of volunteerism and would commit to the project. It is a requirement that COMBAT members in a given community are composed equally of men and women. Whilst literacy is not a requirement for membership in the COMBAT, it is important to have at least one literate member to ensure that there is somebody available to handle the required documentation. Again, while no age limit has been set, the average age of members is generally about 40 years. Depending on the size of the community, the COMBAT membership range between 6 and 10.

#### Training of COMBAT

Once the community has accepted the concept of the RRS and has selected the COMBAT, the process of capacity building begins. The Gender Centre has developed a comprehensive training manual on violence which is used for these trainings and the training is carried out by seasoned facilitators using adult training methodologies. Initially, the COMBAT are given training on VAW, counselling and conflict resolution where they are taught to make available all options to the victim and empower her to take her own decision. COMBAT are made to understand that their role is limited to passing information and that it is the victim who must always take the decision. The in-depth training on VAW focuses on defining violence; explaining violence – including causes and factors such as gender roles and patriarchy, forms and types of violence, impact of violence, and laws in Ghana that deal with violence (Appendix 1). During the five-day training, several exercises are undertaken that allows the trainees to examine and interrogate their own biases and understanding and social norms. Since COMBAT are volunteers, they receive no remuneration from the Gender Centre for their work in the communities. However, refreshments are provided to the COMBAT during all training workshops and meetings.

#### Training of other stakeholders/state agencies

One of the key elements of the RRS is establishing linkages with those state agencies that in one way or the other encounter victims of violence or abuse. Training programs are directed at increasing the capacity of organisations, agencies and individuals to be able to respond to reported and suspected cases of VAW and children. These agencies and organisations include the Police/Domestic Violence and Victim Support Unit (DOVVSU), Department of Social Welfare (DSW), Commission on Human rights and Administrative Justice (CHRAJ) and Ghana Health Service (GHS). The staffs of these agencies are also given the same in-depth training on VAW as the COMBAT.

#### Role of COMBAT in the community

The role of COMBAT is clearly defined and can be summed up as sensitising community on issues on VAW by creating awareness about harmful effects of violence and the benefits of a relationship based on equality. The COMBAT organise public meetings, in churches, during community festivals, association or group meetings and through radio programs. They use various strategies such as role plays to introduce the topic they will be discussing. Once the presentation is made, opportunity is given for the audience to ask questions.

The work of COMBAT is linked to state agencies through a referral system. COMBAT may accompany a victim to report to an agency e.g. GHS, police, DSW, or CHRAJ to support the victim who is engaging with the service for the first time and might be nervous about doing so. The Gender Centre’s experience from prior implementation of the RRS has shown that when a victim of violence seeks outside support, it is important to have other people to be with them, such as family and friends [7]. The COMBAT follows up on cases that have been referred to service provider and the victim herself. Considering the social context within which COMBAT operates, it is stressed that there are certain issues that can only be dealt with by law and that should not be compromised by mediation; but at the same time, COMBAT are taught to respect the victim’s choice and not to force the victim to do something they do not want to do.

#### Post-training support and monitoring

Refresher training for COMBAT and staff of the selected state agencies is provided one year after the initial training while subsequent trainings on counselling, family laws and conflict resolution are carried out every three months. Each COMBAT is supported by an animator who supports the team in system documentation. The animators have a biweekly meeting with COMBAT and are responsible for submitting monthly reports to the Gender Centre project staff. Staff from the Gender Centre are assigned to provide technical support to the COMBAT. This involves bi-monthly meetings with the teams and participating in some of the community sensitisations. In addition, the COMBAT have telephone access to the Gender Centre staff to clarify any issues they may have while on the field. The work of the COMBAT is monitored through quarterly community reflection meetings. The objective of the community reflection sessions is to provide an opportunity for the community members to give their views on the implementation of the RRS and the work of the COMBAT.

#### Study outcomes

The main study outcome is past year incidence of IPV (i.e. perpetration of physical and/or sexual IPV for men and experiences for women) which is assessed with the quantitative survey. The questions and response scale used to asses past 12 months IPV experience or perpetration in our population are listed in Table 1. Secondary outcome indicators in our survey address gender attitudes (women’s subordination, Tolerance of VAW, VAW perpetration, and controlling behaviours), social stigma for the victims of VAW, institutional response to VAW, relevant laws on VAW, women and societal responses to VAW and mental health issues). We report of no changes to the trial outcomes after the trial commenced.

**Table 1. T0001:** Tools for measuring past year IPV experience or perpetration among adult women and men in 4 districts of the central region of Ghana.

*Response scale – If yes, how often did this happen? Never Once, More than once*	
IPV EXPERIENCE BY WOMEN	IPV PERPETRATION BY MEN
**Physical violence by intimate partner**	**Physical violence against intimate partner**
● Was slapped or had something thrown at her that could hurt her	**●** Slapped or thrown something at her that could hurt her
● Was pushed or shoved	**●** Pushed or shoved her
● Was hit with fist or something else that could hurt.	**●** Hit her with fist or something else that could hurt.
● Was kicked, dragged, beaten, choked or burnt	**●** Kicked, dragged beat, choked or burnt her
● Perpetrator threatened to use or actually used a weapons against her	**●** Threatened to use or actually used a weapons against her
**Sexual violence by an intimate partner**	**Sexual violence against an intimate partner**
● Was physically forced to have sex when she did not want	**●** Physically forced to have sex when she did not want
● Had sex when she did not want to because she was afraid of what the partner might do	**●** Had sex when she did not want to because she was afraid of what I might do
● Was forced to do something sexual that she found degrading or humiliating	**●** Forced her to do something sexual that she found degrading or humiliating
● Was forced to watch pornography	**●** Forced her to watch pornography
**Emotional abuse by an intimate partner**	**Emotional abuse against an intimate partner**
● Was insulted or made to feel bad about yourself	**●** Insulted or made her to feel bad about herself
● Was belittled or humiliated in front of other people	**●** Belittled or humiliated in front her of other people
● Perpetrator had done things to scare or intimidate her on purpose (e.g. by yelling or smashing things)	**●** Did things to scare or intimidate her on purpose (e.g. by yelling or smashing things)
● Perpetrator had threatened to hurt her or someone she cared about	**●** Threatened to hurt her or someone she cared about
● Perpetrator boasted about or brought home girlfriend	● Boasted about or brought home girlfriend
**Economic abuse by an intimate partner**	**Economic abuse against an intimate partner**
● Prohibited her from getting a job, going to work, trading or earning money	**●** Prohibited a partner from getting a job, going to work, trading or earning money
● Taken her earnings against her will	**●** Taken a partner’s earnings against her will
● Kept money from her earnings for alcohol, tobacco or other things when he knew she was finding it hard to afford the household expenses	**●** Kept money from your earnings for alcohol, tobacco or other things for yourself when you knew your partner was finding it hard to afford the household expenses

## Study tools

Both qualitative and quantitative measures are used in this trial to evaluate multiple perspectives, contextualise information, and develop a more complete understanding of VAW and IPV in the communities. Quantitative data include standard measures developed by the World Health Organisation for its multi-country study on VAW [6]. These questionnaires have been tested in South Africa over many years in different populations and most recently used in the pilot of Stepping Stones and Creating Futures in South Africa (SS CF pilot) [14,15]. Our trial questionnaires were initially translated into local dialects (Fante and Twi) by an independent consultant and then edited by bi-lingual members of the project team at the University of Ghana. The revised translations were then independently back translated by another consultant who had not seen the English version of the questionnaire. The project team then used a consensus building translation approach to finalise the translated questionnaire. This involved discussing and resolution of discrepancies together with data collectors at the baseline training.

The qualitative component is intended to provide in-depth understanding of the effects of the COMBAT intervention, if any, at individual, community as well as institutional levels. Qualitative data collection was done at baseline and will be repeated at midpoint and the endpoint of the intervention in both intervention and control communities. Focus group discussions (FGDs) are designed to capture perceptions of the community on VAW as well as the components of the proposed intervention. Community members are engaged for the examination of group norms and acts regarding VAW in various contexts. FGD participants may be IPV victims, perpetrators or neither. They may or may not have also been involved in the baseline survey. FGDs are organised separately for women and men to allow for expression of gendered views within a comfortable and convenient environment without any apprehension. All FGDs are gender-matched, where male and female research assistant’s moderate male FGDs and female FGDs, respectively. COMBAT Members’ programmatic perspectives are also captured using FGDs to understand the activities regarding awareness creation on gender-based violence as well as support provided to victims of violence. In-depth interviews (IDIs) are conducted among community members who have had previous VAW experiences (identified from the baseline quantitative survey). Focusing on such individuals allow us to capture-specific VAW experiences in these communities and examine how these experiences highlight the knowledge and understanding of the negative impact of VAW as a social issue as well as actions taken. We plan to engage the same community members at the various data collection points to not only capture changes in knowledge levels, but also to assess the recurrence of VAW acts and individual responses to such recurrence.

Key Informant Interviews (KIIs) are conducted with critical stakeholders and decision-makers in institutions mandated to address VAW cases within the various communities. These key personnel are interviewed for their perspectives on relevance, effectiveness, strengths and weaknesses of the program and the current response mechanisms, and their recommendations for improvement. The interviews also provide useful information on performance of institutional structures, best practices, and collaborations and partnership that are in place to ensure effectiveness of the intervention delivery and sustainability. We further review institutional documents of the critical state agencies mandated to handle VAW issues. Institutional documents used for capturing reports of VAW cases as well as actions taken on such reports are sourced and reviewed from both the intervention and control sites. Details of all cases reported between, 2015 and 2018 will be extracted including number of cases reported, who is reporting information, follow-up on cases reported, recurrence of VAW, etc. Data gathered through document reviews will be triangulated with information from the KIIs, IDIs and FGDs.

## Data collection

### Pre-data collection activities

Pre-data collection fieldwork was carried out in three phases; mapping of study area, pre-testing of data collection instruments, and community mobilisation. Mapping of localities was facilitated by Enumeration Area data obtained from the Ghana Statistical service. Listing of all households in the selected localities was undertaken by trained research assistants and this was used for the computerised random selection of participating households. Cognitive testing of questionnaires was also undertaken to ensure understandability and check appropriateness of responses, including Likert scale options. The questionnaires were pre-tested in a population with the same characteristics as the study population prior to main data collection period. Pre-testing enabled us to test the clarity and suitability of the questions and the results led us to make appropriate changes to the tool. Prior to baseline data collection, community mobilisation, led by the Gender Centre was done to introduce the research in the study sites and to facilitate the recruitment of participants.

## Ethics

Ethical approval for this trial was obtained from the Institutional Review Board at the Noguchi Memorial Institute for Medical Research at the University of Ghana (# 006/15–16) and the South African Medical Research Council’s Ethics Committee (EC031-9/2015). Our research procedure agrees with the ethical principles outlined by the World Medical Association Declaration of Helsinki [16] and the Belmont report [17]. Our trial has been designed to ensure that the project does not expose participants to more than minimal risk (adverse consequences i.e. emotional or psychological harm). We also recognise that complete privacy is essential for ensuring the security of the respondent and the interviewer. Asking about or reporting violence, especially in households where the perpetrator may be present at the time of interview, carries the risk of further violence. Accordingly, our interviewers were provided specific training for implementing the domestic violence module to enable the field staff to collect violence data in a secure, confidential, and ethical manner. The same approach will be followed during the other data collection phases of the trial.

### Informed consent

All research participants provided written informed consent before enrolling in the trial. Participants were informed of the purpose of the trial, trial procedures, potential risks and benefits of the trial and with their rights as participants explained to them. The participant information and consent document are written in simple English, however, to enhance understanding, a researcher is present throughout the informed consent process to clarify any questions the participants were not clear about. Those consenting, signed (or placed a thumb print on) an informed consent form before participating in trial procedures.

### Confidentiality and anonymity

All participants were assured that the information provided will be handled confidentially and that findings will be reported with complete anonymity. This trial uses interviewer –administered tablets for collecting the quantitative data. Electronic handheld devices have been used by the investigators in previous VAW research with young and adult men and women in Ghana, South Africa and elsewhere with great success with both literate and illiterate people [18,19]. Use of electronic hand-held tablets in this trial ensures anonymity of information given by participants as they do not write their names in the tablet. Participants were given unique study codes that are not linkable to their names and thus their responses cannot be traced back to them. Whilst the trial includes questions about engaging in illegal domestic violence activities, we do not collect adequate information about any act in the questionnaire to enable a prosecution of any crime.

### Harm due to trial participation

As part of the trial procedures, we collect information on risks related to the trial. While it is probable that there may be deaths of participants during the trial period, it is highly unlikely for these deaths to be trial related as we will not be administering medication to participants. Notwithstanding this, if a death of the participant occurs, we will promptly investigate on the circumstances and cause of death and a report will be sent to the ethics committees whether the death is found to be trial related or not. This research includes many sensitive topics. It has been well established that there is a potential for harm to participants in research on gender-based violence. The most important concerns relate to the risk of re-victimisation of women who will participate in this trial; and the risk of psychological distress to participants through being asked to re-remember traumatic events. The WHO guidance on safety in conduct of gender-based violence research recommend that the nature of the research be concealed from non-interviewees [20]. Research from diverse global settings has shown that women victims of violence are saddened by talking about their exposure to violence but overwhelmingly they welcome a chance to talk and many describe the research interview as a life-changing occurrence [13,19–22]. Additional research has shown that if these guidelines are followed, there are minimal risks attached to survey research on gender-based violence [15,20]. We have strictly adhered to this guidance in this trial, however, in cases where participants demonstrate distress or report being emotionally impacted by the research questions or intervention, they will be provided with referrals to professional services available in their communities.

### Participant compensation

All participants receive a cash compensation of 10 GHC (~ $3USD) for participating in the trial. No incentive is provided for intervention participation and this is explained to the participants in the intervention arm prior to their enrolment in the study. We are comfortable with this participant compensation approach as research elsewhere has shown that financial incentives alone are not enough to prevent violent experiences or practices [14,15] and so we anticipate that we can meaningfully incentivise both study arms without interfering with the study main outcome.

## Data analysis

The main trial analysis will be done by intention to treat. Thus, for intervention districts, data for all respondents will be included whether they report contact with the intervention or not. Any participant who responds affirmatively to any one of the five questions on physical IPV or three questions on sexual IPV in the past 12 months at end line data collection point will be deemed to be an incident case of IPV victimisation (if woman) or perpetration (if man). IPV incidence will be compared between the study arms. Generalised Linear Mixed model for binary outcome (logistic regression) will be used to compare women’s past year experience or men’s perpetration of IPV between the two arms at end-point, adjusting for baseline prevalence. All qualitative data will be coded, and thematic approach will be used to evaluate the impact of the interventions implemented within the communities.

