### Study design

The study is a mixed method unmatched cluster randomised controlled trial with two arms. The intervention arm receives the rural response system (RRS) intervention for preventing VAW for 18 months while the control arm received no intervention. Owing to the nature of the intervention, participants will not be blind to their trial arm. Sampling of participants will follow a repeat-cross-sectional community survey. The trial is being conducted over 36 months with one quantitative and qualitative baseline assessment (2016) and one qualitative midpoint evaluation (2017). The impact assessment components (both quantitative and qualitative) will occur at 24 months post-baseline (2018). Our trial protocol has been registered and is available on ClinicalTrials.gov (NCT03237585). We did not make any important changes to the trial design after trial commencement.

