#### Selection and randomisation of study sites

The selection of intervention and control districts was done using a census map of the Central Region that showed Inland and Coastal districts. After excluding some districts because of previous VAW-related intervention activities conducted by the Gender Studies and Human Rights Documentation Centre (Gender Centre; two inland and two coastal districts were then purposively selected as study sites. Designated sites are separated from each other by a geographical buffer (at least one district wide) to reduce the possibility of intervention diffusing into control districts (Figure 1). To randomise the districts, the names of the two Inland districts were written on a piece of paper and placed in a bag. One paper was blindly drawn from the bag and the selected district was assigned as an intervention district, while the other was designated as the control district. Clusters in the Ghana Demographic and Health Survey (DHS) are census listed localities with each locality comprising one or more Enumeration Areas (EAs). Within each selected district, a list of localities was obtained from the Ghana Statistical Service (GSS). All localities were allocated numbers, placed in a bag and blindly drawn. A total of 40 localities, (10 per district) were selected to serve as clusters. Since localities comprise several EAs, there was a second layer of stratification such that within each district, women and men participants were drawn from different localities(Figures 2a & b).

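### Districts were allocated within inland and coastal pairs, but the design is called unmatched and the stated primary model leaves the zone out

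*Protocol article*

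**What the plan says.** Under Selection and randomisation of study sites, "two inland and two coastal districts were then purposively selected as study sites". Allocation then took place inside a zone: "To randomise the districts, the names of the two Inland districts were written on a piece of paper and placed in a bag", and "One paper was blindly drawn from the bag and the selected district was assigned as an intervention district", with the other becoming control. Only the inland draw is written out. The same procedure on the coast is implied, because each zone supplies two districts and there are two arms.

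Localities were sampled afterwards: "A total of 40 localities, (10 per district) were selected to serve as clusters". Furthermore, "within each district, women and men participants were drawn from different localities", so each sex-specific analysis uses only part of the 40.

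The Study design section nevertheless says: "The study is a mixed method unmatched cluster randomised controlled trial with two arms". The Abstract uses the same label, and Sample size estimation applies the unmatched Hayes and Bennett method. Data analysis specifies a mixed logistic model comparing IPV "between the two arms at end-point, adjusting for baseline prevalence". It names no other covariate and does not say whether the random effect is for locality or district.

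**The concern.** One inland and one coastal district go to each arm, so zone is balanced between arms by construction. A zone difference in IPV therefore cannot bias the comparison. If the model ignores zone, however, that balanced difference stays in the between-locality error. Study setting gives the zones different economies (cocoa and oil palm inland; pineapple, grain and fishing on the coast), so some difference is plausible, although no IPV figure by zone is given.

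At stake are some precision and a correct account of the design. A reader told that the design is unmatched would not know that zone constrained the allocation, or that it belongs in the model.

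**Working it through.** **Inputs from the protocol.** Control proportion p0 = 0.349; 30% reduction, so p1 = 0.2443; k = 0.20 between localities; two-sided alpha 0.05; 820 per sex per arm. Splitting the localities evenly by sex (an assumption) gives 10 per arm per sex, 5 per district, with n = 820/10 = 82.

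**Inputs not in the protocol (assumed).** Share f of between-locality variance lying between zones, 0 to 0.50; share g lying between districts within a zone, 0 to 0.50; baseline-endline correlation of locality effects, 0.5 to 0.8.

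**The plan's own figure.** Hayes-Bennett: c = 1 + (1.960 + 1.282)² × V / (p0 − p1)², where V = p0(1−p0)/n + p1(1−p1)/n + k²(p0² + p1²).
- Sampling part: 0.00277 + 0.00225 = 0.00502.
- Locality part: 0.04 × (0.1218 + 0.0597) = 0.00726.
- V = 0.01228, so c = 1 + 10.51 × 0.01228/0.01096 = 12.8.

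With 10 localities per arm, power is about 81%, so the stated 90% is not reproduced for the sex-split design. With 20 clusters of 41 it is 93%. That is a separate matter; 81% serves here only as the starting point.

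**Effect of omitting zone, before baseline adjustment.** SE without zone = √(V/10) = 0.0350. SE with zone = √[(0.00502 + (1−f) × 0.00726)/10].

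| f | SE with zone | Excess of SE without zone | Simulated type I error without zone |
|---|---|---|---|
| 0 | 0.0350 | 0% | 0.050 |
| 0.10 | 0.0340 | 3% | 0.044 |
| 0.25 | 0.0324 | 8% | 0.032 |
| 0.50 | 0.0294 | 19% | 0.017 |

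With zone in the model, type I error stays near 0.05. The zone gap implied by f is 2 × √f × 0.20 × 0.349, which is 6.2 points at f = 0.20 and 9.9 points at f = 0.50.

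**After adjusting for locality baseline prevalence, as the plan intends.** These are simulations of a linear model on locality proportions, with a stable zone gap and no district variation within zones.
- f = 0.20: type I error without zone about 0.046; adding zone gains 0 to 1 point of power (for example 84.2% to 85.3% at correlation 0.5, and 89.5% to 89.9% at 0.8).
- f = 0.50: type I error 0.037 to 0.043; gain about 1 to 3 points.
- f = 0: adding zone costs at most about half a point of power.

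**District variation within zones.** With two districts per arm, the true SE without a zone effect is √[(0.00502 + (1−g) × 0.00726)/10 + g × 0.00726/2]. At g = 0.10 this is √(0.001156 + 0.000363) = 0.0390, so the locality-level 0.0350 is only 0.90 of it. At g = 0.05, 0.25 and 0.50 the ratios are 0.95, 0.79 and 0.68.

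Simulated type I error of the locality-level test:

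| f | g | Baseline adjusted | Without zone | With zone |
|---|---|---|---|---|
| 0.25 | 0.10 | no | 0.064 | 0.091 |
| 0.25 | 0.25 | no | 0.115 | 0.158 |
| 0.20 | 0.10 to 0.20 | yes | 0.056 to 0.070 | 0.063 to 0.088 |

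The last row applies when district differences are the same at both surveys. If they drift between surveys, baseline absorbs less of them and the error is larger.

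A test on the two district pairs holds 0.05, but has 1 degree of freedom (critical t 12.71). The two draws allow 2 × 2 = 4 allocations, so the smallest two-sided randomisation p-value is 2/4 = 0.5.

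**The case against.** Four objections deserve weight.

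- **Baseline prevalence already absorbs much of a stable zone difference.** This stands. The 0.017 in the unadjusted table does not describe the planned model; the baseline-adjusted figures do. Absorption is incomplete, because the surveys are repeat cross-sections and each locality's baseline value is an estimate from about 82 people.
- **The standard error is more likely too small than too wide.** A reader might infer from the missing zone term that the interval is too wide and the test conservative overall. The document does not support that. Districts were randomised, and the conservative reading needs districts within a zone to be alike, which nothing in the protocol shows. Where they differ, the zone term raises type I error somewhat, because it removes variation that was masking the missing district component.
- **A full covariate list may sit in an analysis plan.** This is fair, and silence alone would be weak evidence. The conflict between the unmatched label and the paired draw is internal to the article and does not depend on another document.
- **The degree of freedom may not be cheap.** If the random effect is for district, adding zone cuts the degrees of freedom from 2 to 1 and raises the critical t from 4.30 to 12.71. The small cost quoted here therefore applies to a locality-level model.

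**Conclusion.** The mismatch between allocation and description is firm. The statistical cost of leaving zone out is real but small and conditional. It assumes a locality-level model, an even sex split, a zone share of 20% to 50%, a survey-to-survey correlation of 0.5 to 0.8, and no district variation within zones. Under those conditions type I error is about 0.037 to 0.047 and 0 to 3 points of power are lost. If the zones do not differ, nothing is lost.

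No conclusion follows about the overall width of the interval. District variation within zones acts in the opposite direction and can outweigh the zone effect, and a zone term does not repair inference from four randomised districts. The change is worth making because it is cheap and makes the analysis follow the allocation, but only together with a plain statement of the four-district limit.

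**What to change.** - In the Abstract, Study design and Sample size estimation, replace the unmatched label with a description of randomisation by district within inland and coastal pairs, and state how the coastal pair was drawn.
- Add inland/coastal as a fixed effect beside baseline prevalence in the primary models for women and for men, and name the level of the random effect.
- Show the estimated effect in each pair descriptively.
- State that districts, two per arm, are the randomised units, so locality-level intervals and p-values assume negligible district variation within zones.

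The cost is a few wording changes and one model term. In a locality-level analysis the term uses one degree of freedom (18 to 17 before baseline adjustment) and at most about half a point of power if the zones are alike. The downside is slightly less masking of the anticonservatism from district variation, which is why the last statement must accompany the term.
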